### Sample size, power, and non-inferiority

In relation to possible harm to academic performance as an adverse event of long term use of sit-to-stand desks, we will investigate (non-)inferiority, rather than the effectiveness of sit-to-stand desks on measures of academic performance. For this, the 95% confidence interval (CI) and a margin of non-inferiority (the maximum acceptable extent of non-inferiority of an experimental treatment) are relevant. For the following calculations we have used the expected 20 students per group, and the distribution data of academic performance provided by CITO [https://www.cito.com]. Note that the data of the school participating in this study are similar to the data provided by CITO:

$$ \mathrm{We}\ \mathrm{assume}:{\mathrm{n}}_{\mathrm{exp}}={\mathrm{n}}_{\mathrm{con}}=20\ \mathrm{and}\ \mathrm{equal}\ \mathrm{variance} $$

**Table Taba:** 

	Reading comprehension	Arithmetic	Orthography
Mean	159	214	214
SD	25	26	26
SE diff	7.9	8.3	8.3
95% CI diff	15.8	16.6	16.6
% mean	10	7.8	7.8

This means that for accepting non-inferiority in case μ = 0 or μ > 0, at maximum a difference between the mean scores of both groups of around 10% will be accepted. If μ < 0 (i.e., the mean score of the experimental group is more than 10% lower than the mean score of the control group), non-inferiority will not be accepted.

With regard to the proportion of sitting time (i.e., second primary outcome), we look at the effectiveness of sit-to-stand desks. For these calculations we used the results from the study by Clemes et al. [17]. We used the pooled statistics of the follow-up assessment of the control groups in this study to calculate the 95% CI. Based on these results, chances are small that in this study, with an expected 20 participants in each group, a significant difference in sitting time will be found between groups at the end of the study (i.e., the α-approach). The lower and upper limits of the 95% CI (H_0_) are 59.9 and 70.2 respectively, with an expected mean of 60.3 for the experimental group. However, we may fail to detect a difference when actually there is a difference (i.e., the β-approach). Following similar differences between experimental and control groups in the Clemes et al. [17] study, this probability of failing to detect a difference when actually there is a difference is almost 50% (β = 0.54; power = 0.46).

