### Recruitment

Students of two grade-three groups (aged 8–9 years) following regular primary education were recruited from a school in Leiden, The Netherlands, of which the school director initiated this study. At this school there were four grade-three groups. The common group size is 26 to 30 students. The deputy director of the school selected two groups in consultation with the teachers, based on the willingness of the teachers to be involved in the study. All children in both groups were asked to participate. The allocation was only established after baseline assessment (which was after informed consent). In order to be eligible to participate in this study, a student had to meet all of the following criteria:
Follow regular primary education in third gradeHave a signed Informed Consent form to participate; given the age, parents/caregivers should sign the Informed Consent form for their child but the student will be asked to sign one as wellBe physically able to stand without any serious health issues or injuries; note that a student who is normally physically able to stand, but temporarily unable to do so because of a recovery from a temporary injury of trauma, can still participate in this study

Students who object to participate are not included in the study. Examples of objection are (signals of) fear, sadness, and anger. We expected to recruit around 20 students per group. Students who did not participate from the start of the study, but wish to do so at a later moment, are also enrolled at the next moment of testing. Those who terminate their participation before the end of the study are asked for the reason(s) why. Demographics of students that in fact are recruited (and for whom we received written informed consent from themselves and their parents/caregivers) are presented in Table 1.

**Table 1 Tab1:** Participants’ age and sex

	Control group	Intervention group	Total
	(n = 19)	(*n* = 19)	(*n* = 38)
Years of age median [range]	9.0 [8.5 to 10.2]	8.9 [8.5 to 10.3]	8.9 [8.5 to 10.3]
Girls n (%)	10 (52.6)	11 (57.9)	21 (55.3)

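### The non-inferiority margin for academic performance is taken from the trial's own expected precision, is stretched to 10% where the table gives 7.8%, and sits in an unclear decision rule

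*Protocol article*

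**What the plan says.** The Background makes possible harm to academic performance the primary aim. The section Sample size, power, and non-inferiority says that two things matter for this: the 95% confidence interval and "a margin of non-inferiority (the maximum acceptable extent of non-inferiority of an experimental treatment"). It then gives the basis of the calculation: "For the following calculations we have used the expected 20 students per group", together with "the distribution data of academic performance provided by CITO".

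The unnumbered table in that section covers reading comprehension, arithmetic and orthography, in that order:

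- means: "Mean 159 214 214"
- standard deviations: 25, 26 and 26
- standard errors of the difference: "SE diff 7.9 8.3 8.3"
- confidence interval half-widths: "95% CI diff 15.8 16.6 16.6"
- half-widths as a percentage of the mean: 10, 7.8 and 7.8

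The next sentence presents the margin as what follows from this table: "at maximum a difference between the mean scores of both groups of around 10% will be accepted". The text goes on to equate μ < 0 with an experimental mean score more than 10% below the control mean, in which case non-inferiority is not accepted.

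Recruitment states "We expected to recruit around 20 students per group"; Table 1 shows 19 per group.

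**The concern.** By the article's own definition, a margin is the largest loss one would still accept. That judgement concerns schooling and should not depend on how many children were available. Here the only source offered for the margin is the half-width expected at 20 per group, so the size of the trial sets the harm it tolerates.

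Two further faults are visible in the same place. One rounded percentage is applied to three tests although the table supports it for only one. And the rule is worded on mean scores, while the start of the section points to the confidence interval.

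What is at stake is the main claim of the trial. The Discussion accepts the small sample because the sitting-time calculation was subordinate to the non-inferiority calculation. If the margin has no footing outside the sample size, that argument is circular. A conclusion of non-inferiority could then rest on excluding only large losses, without the reader being told so.

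**Working it through.** **Inputs.** Means 159 / 214 / 214, SDs 25 / 26 / 26, n = 20 per group and equal variances, all from the sample size section; 19 per group from Table 1; two-sided 5% from Statistical analysis.

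**1. Reproducing the table.** SE = SD × √(2/20).

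- Reading: 25 × 0.3162 = 7.91 (stated 7.9). Twice the SE is 15.8 (stated 15.8), and 15.8/159 = 9.9% (stated 10).
- Arithmetic and orthography: 26 × 0.3162 = 8.22 (stated 8.3; an unrounded SD slightly above 26 would explain the gap). Twice the SE is 16.4, and with the t quantile on 38 df it is 16.6 (stated 16.6). 16.6/214 = 7.8% (stated 7.8).

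The table reproduces. It describes precision and nothing else.

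**2. Dependence on sample size.** The same formula for reading, 2 × 25 × √(2/n) / 159, gives 14% for n = 10, 9.9% for n = 20 and 7.0% for n = 40 per group. Fewer children mean a larger permitted loss.

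**3. The flat 10% against the table.**

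| Test | 10% of mean | Table half-width | Ratio | 10% in SDs |
|---|---|---|---|---|
| Reading | 15.9 | 15.8 | 1.01 | 15.9/25 = 0.64 |
| Arithmetic, orthography | 21.4 | 16.6 | 1.29 | 21.4/26 = 0.82 |

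The table half-widths themselves are 15.8/25 = 0.63 and 16.6/26 = 0.64 SD.

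**4. What the two readings of the rule imply.**

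- *Observed means compared with 10%.* An observed deficit of up to 0.64 or 0.82 SD would not be rejected. With a true difference of zero, acceptance is nearly certain: Φ(15.9/7.91) = 0.98 and Φ(21.4/8.22) = 0.995.
- *Lower 95% limit compared with 10%.* The largest observed deficit that passes is about 15.9 − 16.0 ≈ 0 points for reading and 21.4 − 16.6 ≈ 4.8 points (0.18 SD) for the other two. A true loss equal to the margin passes about 2.5% of the time.

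**5. Chance of success under the confidence-limit reading.** Assumptions: true difference 0, unadjusted comparison at one time, 20 per group, no class effect. Normal approximation Φ(margin/SE − 1.96), checked with the noncentral t on 38 df:

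- reading at 15.9 points: 0.52 (normal), 0.50 (t)
- arithmetic and orthography at 21.4 points: 0.74 and 0.72
- arithmetic and orthography at 16.6 points: 0.52 and 0.50

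At 19 per group, the t figures are 0.48 (reading) and 0.70 (the others at 21.4 points).

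**6. Effect of baseline adjustment.** The planned model adds baseline outcomes. With an *assumed* baseline correlation r, the SE shrinks by √(1 − r²). For r = 0.7 to 0.8 at 20 per group, the half-width becomes 11.4 to 9.6 points (reading) and 11.9 to 10.0 (others). The chance of success at the 10% margin becomes about 0.78 to 0.90 and 0.94 to 0.99 (noncentral t), still with no class effect. The documents give no value for r.

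**The case against.** The strongest reply is that the alarming consequences depend on assumptions the article does not make. Much of this stands.

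- A reader might infer that the trial has only even odds of showing non-inferiority. That holds only for an unadjusted comparison under the confidence-limit rule with the margin equal to the half-width. At 10% it is already 0.72-0.74 for two tests, and the planned mixed model with baseline covariates would raise all the figures.
- A reader might infer a low joint chance of success across the three tests. The article nowhere says that all three must pass, so no joint figure is put forward.
- A reader might infer that a loss of 0.64-0.82 SD would routinely pass as harmless. Under the confidence-limit rule it would pass about one time in forty. The inference fits only the literal comparison of observed means.
- Expressing a margin as a percentage of the mean is a choice of scale, not an error in itself.
- The 16.6 points in the table cannot serve as a properly justified margin either, since they come from the same sample size.

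It could also be said that around 10% is deliberately loose wording. Moving from 7.8% to 10% widens the margin by 29%, which is more than rounding. None of these replies supplies a reason for the margin that is independent of n, or settles which rule applies.

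**Conclusion.** The point holds. The article defines the margin as a limit of acceptability but derives it only from expected precision at 20 per group. It then applies 10% to arithmetic and orthography where its own table gives 7.8% (21.4 against 16.6 points). The resulting margins are 0.64 SD for reading and 0.82 SD for the other two tests. These statements need only the table and arithmetic.

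The decision rule is also ambiguous: the two readings in step 4 lead to very different trials, and equating μ < 0 with a deficit above 10% leaves losses between 0 and 10% unclassified.

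The chance-of-success figures are conditional on the assumptions in step 5. The article states power for sitting time (0.46) but no chance of success for the outcome it ranks first. The documents do not show that the trial is bound to fail or to mislead, nor whether a properly justified margin would be stricter or looser than 10%. This is a wrongly fixed threshold for the primary aim, not a detail that could be left to an analysis plan.

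**What to change.** - State that non-inferiority is judged by comparing the lower 95% confidence limit of the difference with the margin, and remove the wording on observed means and μ < 0.
- Before outcome data are analysed, set one margin per test in CITO score points, with a reason that does not involve the number of children. A stated fraction of normal CITO growth over the follow-up would be one route, if such norms are available; the article shows none.
- Label the table as expected precision, not as the margin.
- State the chance of success for the planned baseline-adjusted mixed model at 19 per arm, with the assumed correlation and class effect shown as ranges.

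If no independent justification can be given, do not extend 10% to arithmetic and orthography beyond the table's 7.8%. Say openly that the figures reflect precision, and limit the conclusion to the size of loss that the interval excludes.

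The cost is a short recalculation, some rewording and possibly a less favourable claim. There is also a cost in timing: the last scheduled assessment was July 2019 and children and teachers are not blinded. A revised margin must therefore be dated and labelled as revised, and the result against the published 10% reported beside it.

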### Statistical analysis

The statistical analysis will be conducted in SPSS. A two-tailed significance level of .05 will be used for all tests.

Summary statistics for the baseline measures and participant demographics for both groups will first be examined. Dependent on the variable, the means, medians or frequencies will be compared between both groups using a two-sample T-test, a Mann-Whitney U test or chi-square test, as appropriate.

Outcome data obtained from all students will be included in the data analysis, and data will be analyzed as per group allocation. In our statistical analysis the longitudinal and multilevel structure of the data are acknowledged and will be taken into account in achievement growth modeling. For this, mixed modeling will be used, because this specifically allows for the analysis of repeated measures and nested data. Furthermore, missing data are better handled in mixed modeling. We will first determine the growth (longitudinal changes) for the different outcome measures on an individual and on a group level. In determining the proportion of variance explained by group allocation (i.e., sit-to-stand or regular desks) for sitting time as well as for academic performance (i.e., the primary outcome measures), explanatory variables such as age, gender and baseline outcomes will be added to the model. We will do this both on an individual and on a group level, also for a number of secondary outcome measures. We will test for significance of the effect of group allocation on a group level.

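### The non-inferiority rule for academic performance contradicts itself and sets mean scores, not a confidence limit, against the roughly 10% margin, and the analysis section does not repair it

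*Protocol article*

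**What the plan says.** The Background names harm to academic results as the primary aim. Under Sample size, power, and non-inferiority the article commits to a framework: "we will investigate (non-)inferiority, rather than the effectiveness of sit-to-stand desks on measures of academic performance". It adds that "the 95% confidence interval (CI) and a margin of non-inferiority (the maximum acceptable extent of non-inferiority of an experimental treatment) are relevant".

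An untitled table then derives the half-width of a 95% interval for the group difference with 20 pupils per group. The decision rule follows the table. Its accepting clause covers μ equal to or above zero and tolerates a gap of around 10% between the mean scores. Its refusing clause covers μ below zero, explained in brackets as the situation in which "the mean score of the experimental group is more than 10% lower than the mean score of the control group". The article does not define μ.

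The Statistical analysis section describes mixed models for both primary outcomes. Academic performance appears there in this plan: "In determining the proportion of variance explained by group allocation (i.e., sit-to-stand or regular desks) for sitting time as well as for academic performance". The section ends: "We will test for significance of the effect of group allocation on a group level". All tests are two-tailed at .05. The section contains no margin, no confidence-limit criterion and no mention of non-inferiority.

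**The concern.** A non-inferiority claim needs the data to rule out harm as large as the margin. That is a statement about a confidence limit. The bracketed explanation instead asks only whether one mean falls more than 10% below the other, which takes no account of sampling error. It also does not match the condition it explains, because a 5% deficit makes μ negative but is not more than 10% lower.

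The analysis section does not settle the matter. A significance test of allocation asks whether the difference is zero, and a variance share has no direction and no margin. Neither answers the primary question.

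The Discussion accepts the small sample because the harm question takes precedence, and the Background offers the findings to policy makers. An unclear or lenient criterion here affects the main conclusion of the study.

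**Working it through.** **Inputs.** From the table under Sample size, power, and non-inferiority: "Mean 159 214 214" for reading comprehension, arithmetic and orthography; SDs 25, 26 and 26. On group size: "For the following calculations we have used the expected 20 students per group". The margin is about 10% of the mean, so 15.9 points for reading and 21.4 for the other two. Table 1 under Recruitment shows 19 per group enrolled.

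**1. The plan's own figures.** SE = SD × √(2/n).
- Reading: 25 × √(2/20) = 7.91. Twice this is 15.81, or 9.9% of 159. The table gives 7.9, 15.8 and 10.
- Arithmetic and orthography: 26 × √(2/20) = 8.22. Twice this is 16.44, or 7.7% of 214. The table gives 8.3, 16.6 and 7.8, about 1% higher.

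The table therefore reproduces closely.

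**2. The rule, applied to an observed difference d (experimental minus control).**
- d at or above 0: accepted.
- d between −10% and 0: μ is negative, so the acceptance condition fails; but the bracketed definition of refusal is not met either.
- d below −10%: refused.

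The middle band has no consistent verdict.

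**3. Bracketed clause taken literally (refuse only below −10%).** P(accept) = Φ((margin + true difference)/SE).
- True difference = −margin: Φ(0) = 0.50 for each test, whatever the SE. Simulating an experimental mean of at least 0.9 times the control mean (200,000 runs) gave 0.499 for reading and 0.500 for arithmetic.
- True harm of 12% of the mean: Φ(−3.18/7.91) = 0.34 for reading; Φ(−4.28/8.22) = 0.30 for arithmetic and orthography.

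**4. Confidence-limit rule (lower 95% limit above −margin), pupils independent.** P(accept) = Φ((margin + true difference)/SE − 1.96).
- True difference = −margin: 0.025.
- True harm of 12%: 0.009 and 0.007.
- True difference 0: Φ(15.9/7.91 − 1.96) = 0.52 for reading; Φ(21.4/8.22 − 1.96) = 0.74 for the other two. With 19 per group these become 0.50 and 0.72.
- For 80% power at zero true difference: 39 per group (reading) and 24 (arithmetic, orthography).

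**5. Sign of μ taken literally (accept only if d is 0 or more).** At true harm equal to the margin: Φ(−15.9/7.91) = 0.022 for reading; Φ(−21.4/8.22) = 0.005 for the other two.

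**6. Why a significance test cannot stand in.** At a true reading deficit of 15.9 points, a two-tailed .05 test with 20 per group is non-significant 48% of the time. At a deficit of 21.4 points in arithmetic it is non-significant 26% of the time.

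**7. Clustering.** The documents give no intraclass correlation; I assume 0.05 to 0.20. The design effect 1 + 19 × ICC is then 1.95 to 4.8. An interval that ignores it accepts at the margin with probability 1 − Φ(1.96/√1.95) = 0.08 to 1 − Φ(1.96/√4.8) = 0.19, not 0.025. If the SE for reading were widened to match (11.04 to 17.32), power at zero difference would fall to 30% to 15%.

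**The case against.** The strongest reply is that a confidence-limit rule was intended. The section names the interval and the margin, computes the half-width, and introduces the rule as its consequence. If μ is the observed difference and the margin is the half-width, requiring μ to be at least zero is the lower-limit rule for reading. Acceptance at the margin is then about 2%, not 50% (step 5), and the bracketed clause is a slip. This reading is tenable, so a reader should not infer that the trial definitely decides on the observed means. What remains is that the clause contradicts that reading, it is the only explicit criterion, and nothing later corrects it.

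Two further inferences are not supported:
- That the trial would declare no harm about half the time. The 50% is per test, and the article does not say how the three tests combine. If all three had to pass and each had harm at the margin, the chance would run from 0.5³ = 12.5% (independent) to 50% (perfectly correlated). The combination rule can be left to an analysis plan.
- That a non-significant p-value will be reported as no harm. No sentence says so.

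It can also be said that an article need not repeat the non-inferiority test in its analysis section. That is fair as to detail. But the article states a defective rule, and the analysis it describes for the same outcome cannot answer the non-inferiority question. Neither is a matter of omitted detail.

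**Conclusion.** The concern holds as a defect in the written criterion for the primary aim. μ is undefined, its negative case is equated with a deficit above 10%, and the explicit comparison uses mean scores where a confidence limit is needed. The analysis section does not put this right.

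The size depends on the reading. With the bracketed clause applied literally, each test accepts non-inferiority 50% of the time at a true harm equal to the margin, and 34% (reading) or 30% (arithmetic, orthography) at a true harm of 12%. A confidence-limit rule gives 2.5% and under 1%. With the sign of μ applied instead, acceptance at the margin is about 2% for reading and 0.5% for the other two. Two readings of one rule that differ this much are reason enough to rewrite it.

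Apart from the ICC range, these figures use the article's SDs, 20 per group and independent pupils. The 50% does not depend on the SE; the 2.5% does, and it is optimistic with one class per arm.

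**What to change.** Define μ as the experimental minus control difference and delete the bracketed 10% clause. State the same rule in both sections: non-inferiority on a test is concluded only if the lower limit of the two-sided 95% confidence interval for the group difference, taken from the planned mixed model, lies above minus the stated margin. Say that the significance test and the variance explained are not the basis for the academic conclusion.

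The edit itself is a change of wording, but it has two consequences that should be stated openly:
- Non-inferiority becomes hard to show: at zero true difference, power with 20 per group is about 52% for reading and 74% for arithmetic and orthography at a 10% margin, before clustering. Failing the criterion would then be inconclusive and would not by itself show harm.
- With one class per arm, class and desk type are confounded. The mixed model cannot estimate between-class variation separately, so its interval cannot reflect it. Any non-inferiority conclusion must be qualified as applying to these two classes, with that source of error not covered.

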The study also knows some limitations. First, the sample size is most likely too small for detecting a significant difference in sitting time. The downside is that a small sample size limits population estimation and extrapolation of findings. In addition, a possible true effect may be masked by a relatively large variance in our sample (this is the reason why we calculated the probability of failing to detect a difference). On the upside, in the study we use a repeated-measures design instead of the pre-post design that was used in the study by Clemes et al. [17]. This increases the power to some extent. However, given the fact that the primary aim was to assess possible harm to academic performance, the effect of sit-to-stand desks on sedentary time reduction (and the related sample size calculation based on results the study by Clemes et al. [17]) was considered subordinate to the investigation of possible harm to academic performance (and the related non-inferiority calculation). Given the circumstances, we therefore accepted a small sample size, which is around half the sample size of the study by Clemes et al. [17], and we will treat the outcomes with cause.

An additional limitation follows from the group randomization, which is inevitable in studies with school classes. Group randomization has a negative effect on the power of the study. With the proposed statistical analysis (i.e., mixed modeling), we will be able to determine the extent of the negative effect of this design on the power of the study and discuss the consequences.

Furthermore, this study involves only one school. Potential limited external validity and problems with blinding are common limitations in single-center (ic. single-school) studies, which may also apply to this study. We will take these limitations into consideration in our analyses and findings.

The program of “A Good Beginning” started in 2017 and results are expected by the beginning of 2020. The results of this study may provide relevant information to set up a larger scale efficacy trial, possibly with children of different ages (also in secondary education), more schools with different populations, and a protocol focusing primarily on sedentary time reduction.

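### The stated power of 0.46 for sitting time is an individual-level figure that leaves out the class randomization, and the planned mixed model cannot supply the missing correction

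*Protocol article*

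**What the plan says.** In Methods, *Sample size, power, and non-inferiority*, the sitting-time calculation rests on an earlier study of similar desks: "We used the pooled statistics of the follow-up assessment of the control groups in this study to calculate the 95% CI" (the study meant there is the earlier one). The "limits of the 95% CI (H_0_) are 59.9 and 70.2 respectively", "with an expected mean of 60.3 for the experimental group", and the calculation is made "with an expected 20 participants in each group". It ends with the statement that "this probability of failing to detect a difference when actually there is a difference is almost 50% (β = 0.54; power = 0.46". No SD, SE, ICC or design effect is printed for this outcome.

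*Statistical analysis* fixes the test level: "A two-tailed significance level of .05 will be used for all tests". It plans mixed models with baseline outcomes among the explanatory variables, and a test of allocation at group level.

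Under *Design*, allocation is one coin toss between two classes. The limitations in the *Discussion* concede that "Group randomization has a negative effect on the power of the study", and go on to say that the mixed model will show how large that effect is. They also say that the sample is probably too small for sitting time and that repeated measures raise power somewhat.

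**The concern.** The figure of 0.46 is the only power value in the protocol, and it covers the one primary outcome that is tested for effectiveness. It uses the number of children, while the unit of allocation is the class. The protocol acknowledges the resulting loss in words but leaves it out of the number, and defers its size to an analysis that cannot measure it.

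A second uncertainty lies in the interval itself. It is centred on a level of sitting time rather than on a difference of zero, and it was derived from control groups only. If it describes one control mean, that mean has been treated as a fixed target and the comparison lacks the second group's sampling error.

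At stake is how a non-significant sitting-time result will be read. Near-even odds of detection make such a result mildly informative; odds of one in four or fewer make it close to uninformative.

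**Working it through.** **Inputs.** Limits 59.9 and 70.2, expected experimental mean 60.3, and 20 per group (*Sample size, power, and non-inferiority*); two-sided 0.05 (*Statistical analysis*); one class per arm (*Design*).

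**Implied quantities**
- Centre: (59.9 + 70.2)/2 = 65.05. Half-width: (70.2 − 59.9)/2 = 5.15.
- SE: 5.15/1.96 = 2.63. Assumed difference: 65.05 − 60.3 = 4.75.
- Implied SD: 2.628/√(2/20) = 8.31 if this is the SE of a difference; 2.628 × √20 = 11.75 if it is the SE of one mean of 20.

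**Reproducing the printed figure.** Power is the chance that the experimental mean falls below 59.9 when its true value is 60.3.
- One SE throughout: Φ((59.9 − 60.3)/2.628) = Φ(−0.152) = 0.44. Rounding of the printed inputs allows 0.425 to 0.455.
- Limit 59.9 kept, but SE enlarged to 2.628 × √2 = 3.72: Φ(−0.4/3.72) = 0.457, so β = 0.543. This matches the printed 0.46 and 0.54.
- Interval built with t on 38 df (SE 2.544) and a normal power step: Φ(4.75/2.544 − 1.96) = 0.463. This also rounds to 0.46.

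More than one route reaches 0.46, and every one treats the children as independent.

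**Coherent two-sample power under independence**, Φ(4.75/SE − 1.96)
- Reading A, the interval is that of the difference: Φ(4.75/2.628 − 1.96) = 0.44.
- Reading B, the interval is that of one control mean: Φ(4.75/3.716 − 1.96) = Φ(−0.68) = 0.25.
- With the 19 per arm in Table 1 (*Recruitment*), these become 0.42 and 0.24.

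**Adding clustering.** SE is multiplied by √(1 + 19 × ICC) for 20 children per class. The ICC values are assumptions, and no gain from baseline adjustment or repeated measures is included.

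| Assumed ICC | 1 + 19 × ICC | Reading A | Reading B |
|---|---|---|---|
| 0 | 1.00 | 0.44 | 0.25 |
| 0.01 | 1.19 | 0.38 | 0.22 |
| 0.02 | 1.38 | 0.34 | 0.19 |
| 0.05 | 1.95 | 0.25 | 0.15 |
| 0.10 | 2.90 | 0.18 | 0.11 |
| 0.20 | 4.80 | 0.13 | 0.08 |

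Example, reading A at ICC 0.05: √1.95 = 1.396; 4.75/(2.628 × 1.396) = 1.294; Φ(1.294 − 1.96) = 0.25.

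**Can the mixed model measure the loss?** The contrast between arms equals the desk effect plus the difference between two class effects. There is one such contrast and no second class within either arm, so there are 2 − 2 = 0 between-class degrees of freedom. The between-class variance, and with it the ICC, cannot be estimated apart from the treatment effect. The table therefore presumes an ICC known from elsewhere.

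Analysing the children as independent does not avoid the problem. The actual type I error would be 2 × (1 − Φ(1.96/√(1 + 19 × ICC))), which is 0.16 at ICC 0.05 and 0.25 at ICC 0.10.

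**The case against.** The strongest reply is that the protocol is candid. It says beside the power figure that a significant difference is unlikely, and its limitations name the small sample, the cost of group randomization and the lower priority of sitting time. A reader might infer that low power has been concealed; the documents do not support that. What remains is that the warnings give only the direction, while the number stands uncorrected.

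A second reply is that the analysis is stronger than the calculation. Baseline outcomes enter the model, and six assessments are made. This has force. If the baseline correlation is assumed to be 0.5 and the SD is scaled by √(1 − 0.5²), power at ICC 0.05 rises from 0.25 to 0.32 on reading A and from 0.15 to 0.18 on reading B. With an assumed correlation of 0.7, reading A at ICC 0.05 returns to 0.44. Baseline adjustment can also remove a stable class difference already present at T0. It cannot remove a later divergence between the classes that has nothing to do with the desks. The printed 0.46 includes neither this gain nor the clustering loss, so the one cannot be used to defend it.

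A third reply is that on reading A the arithmetic is nearly right (0.44 against 0.46), and the difference is within what rounding and choice of quantile can produce. That is correct. The large gap under independence (0.25) depends on reading B, and the SD that would settle the matter is not printed.

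**Conclusion.** The point stands in a limited form. The value 0.46 is an individual-level power that omits the class allocation, and the statement that mixed modelling will reveal the extent of the loss cannot be fulfilled with two classes.

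Under independence, power is about 0.44 or 0.25, depending on what the interval describes. The control-only source and the close match at 0.457 favour the single-mean reading, but another route also gives 0.46, so it is not established.

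A reader might go on to infer that the design delivers roughly 0.08 to 0.25. The documents do not support that as a fact. It needs assumed ICCs of 0.05 to 0.20, the lower end also needs the single-mean reading, and the planned baseline adjustment and repeated measures are left out. An ICC of 0.01 to 0.02 gives 0.38 to 0.34 on reading A. The defensible statement is conditional: for assumed ICCs of 0.01 to 0.20, without those gains, about 0.38 to 0.13 on reading A and 0.22 to 0.08 on reading B.

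**What to change.** In *Sample size, power, and non-inferiority*:
- Print the SD taken from the earlier study, and say whether the interval is that of one mean or of a difference.
- Replace 0.46 with a coherent two-sample calculation, labelled as individual-level and ignoring clustering.
- Follow it with the power range over a stated set of ICCs, labelled as assumption-based. If credit is taken for baseline adjustment or repeated measures, state the assumed correlation.

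In the *Discussion* limitations:
- Replace the promise that mixed modelling will determine the power loss with the statement that two classes cannot estimate it.
- State that a non-significant sitting-time difference will be reported with its CI as inconclusive.

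The cost is a few sentences and a less favourable stated figure. No extra children, visits or measurements are needed.
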